#### Fidelity and acceptability

Fidelity/adherence data will be derived from training completion rates and the process evaluation. Acceptability of the intervention is pre-specified as > 70% of health provider participants rating the intervention ‘completely acceptable’ at 9 months [40].

#### Process analysis

Qualitative data collected during the process analysis interviews and observations will be thematically analysed using an inductive and reflexive coding approach to iteratively revise and define semantic themes [41] and managed through NVivo. Revisions to the Theory of Change will be iteratively discussed by the research team, and a final determination of the Theory of Change will be reached by team consensus.

#### Economic analysis

We will undertake a trial-based analysis to describe the additional costs (savings) and consequences arising from our intervention as compared to our usual care control condition. The cost-effectiveness analysis will capture two types of costs: (1) participant direct medical (primary and allied health care, medications, acute and subacute admissions) and social care costs (paid and unpaid home care and transitions to residential care) estimated from an adapted RUD-lite [42] plus supplementary self-report at baseline, 4 months, and 9 months and (2) costs associated with implementing the intervention and control conditions estimated from administrative and fidelity data. We will relate cost per participant to patient-level measures of safety, quality of life, and mental health. In line with the main analysis, the primary outcome for the economic evaluation will be social care quality adjusted life-years (QALYs) to final follow-up calculated based on ASCOT scores [31, 43] at baseline, 4 months, and 9 months. The secondary outcome for the economic evaluation will be health QALYs to final follow-up calculated based on SF12v2-based SF6D scores [44] at baseline, 4-month, and 9-month data. Following recent recommendations [45], results will be expressed as (i) cost per ASCOT-based social care QALY and (ii) cost per SF6D-based health QALY. We will summarise sampling error and decision uncertainty using the bootstrap acceptability method to calculate confidence intervals and generate cost-effectiveness acceptability curves [46].

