### Sample size

As health providers are not anticipated to be systemically different based on location (clusters), we have not accounted for ICC for health providers; therefore, we calculated that 60 health providers would be sufficient to detect a medium effect (Cohen’s *d* of 0.5) on the KAMA at a power of 80% and a significance level of 1%. This difference is similar to that reported in our previous research, and the sample size calculation uses a standard deviation of 4.8 as previously reported [34]. We calculated that we need 10 clusters (5 intervention, 5 control) with 40 older people in each cluster to detect a medium effect on the ASCOT at a power of 80% and a significance level of 5%. As responses to elder abuse vary across jurisdictions, an ICC of 0.1 is assumed for older people with the standard deviation of 0.2 reported by others [35], calculated using the Shiny Calculator for Sample size for Cluster Randomised Trials [36]. Assuming 53% refusal rate to participate/unable to consent as observed in our group’s prior work in the UK [37, 38], the total sample size is 92 health providers and 612 older people (~ 60 older people/site).

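### The economic bootstrap has no stated allowance for the 10 randomised sites, and with 5 sites per arm both plain ways of running it give intervals that are too narrow

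*Protocol article*

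**What the plan says.** The trial randomises sites. For older people, the Sample size section of the protocol article states that "we need 10 clusters (5 intervention, 5 control) with 40 older people in each cluster to detect a medium effect on the ASCOT", and that "an ICC of 0.1 is assumed for older people". After allowance for refusal the recruitment target is 612, or about 60 per site.

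Under Primary and secondary RCT outcomes, both primary outcomes are analysed with mixed models that carry random effects for participant and for site. Secondary outcomes are to be handled in the same way.

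The Economic analysis section is separate. Its primary outcome is the social care QALY, built from ASCOT scores at baseline, 4 and 9 months. Its secondary outcome is a health QALY from the SF-6D. It says "We will relate cost per participant to patient-level measures of safety, quality of life, and mental health". On uncertainty it says "We will summarise sampling error and decision uncertainty using the bootstrap acceptability method to calculate confidence intervals" and to produce acceptability curves. It does not say whether participants, sites, or participants within sites are resampled, and it does not mention clustering.

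**The concern.** The same patients, sites and ASCOT scores get a site effect in the clinical analysis and no stated allowance in the economic one. The phrase in the economic section that aligns it with the main analysis concerns the choice of outcome, not the model.

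A bootstrap that draws participants as if independent sees only the variation between people. The arm comparison also varies with which 5 sites fall in each arm. The cost side is exposed too: each site has a champion for one day a week, and implementation costs are to come from administrative and fidelity data, so part of the cost arises by site.

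At stake is how certain the cost per QALY appears. Intervals for the cost and QALY differences would be too narrow, and the curves would move too quickly towards 0 or 1.

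**Working it through.** The article gives no figure for the precision of the economic results, so there is none to reproduce.

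**Inputs.** From Sample size: 5 sites per arm, m = 40 people per site in the calculation, about 60 per site as the recruitment figure (612/10 = 61.2), and an ICC of 0.1. That ICC is a planning value for the ASCOT. None is given for costs, ASCOT QALYs or SF-6D QALYs, so the range 0.01 to 0.10 is an assumption.

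**Reading 1: participants are resampled and site is ignored.** The true standard error divided by the bootstrap standard error is about sqrt(DE), where DE = 1 + (m − 1) × ICC. At m = 40 and ICC 0.1, DE = 1 + 39 × 0.1 = 4.9 and sqrt(4.9) = 2.21.

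| ICC | m = 40: DE, factor | m = 60: DE, factor |
|---|---|---|
| 0.01 | 1.39, 1.18 | 1.59, 1.26 |
| 0.02 | 1.78, 1.33 | 2.18, 1.48 |
| 0.05 | 2.95, 1.72 | 3.95, 1.99 |
| 0.10 | 4.90, 2.21 | 6.90, 2.63 |

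The approximate coverage of a nominal 95% interval is 2Φ(1.96/factor) − 1. At a factor of 2.21 this is 2Φ(0.885) − 1 = 62%. At 1.33 it is 2Φ(1.47) − 1 = 86%.

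**Reading 2: whole sites are resampled.** With k = 5 sites per arm, the variance of a plain site bootstrap is too small by (k − 1)/k = 4/5, so its standard error is 0.894 of the right value. A percentile interval also uses roughly normal limits where a t distribution on 8 degrees of freedom applies. Coverage is about P(|t8| < 1.96 × 0.894) = P(|t8| < 1.75) = 88%.

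**Simulation.** Trials were simulated with normal outcomes, 5 v 5 sites of 40 and no true difference, using percentile intervals.

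- Participants resampled: standard error ratio 2.2 to 2.3 and coverage 61 to 64% across separate runs at ICC 0.1; coverage about 86% at ICC 0.02.
- Whole sites resampled: coverage about 87 to 90% over ICC 0.01 to 0.10.
- Two-stage with shrinkage correction: standard error ratio about 1.0 and coverage about 91 to 95% over the same range. The lower end is at ICC 0.1, as expected from P(|t8| < 1.96) = 91%.

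The simulation used normal data. Real costs are skewed, so these coverages show the size of the clustering problem and do not predict the trial's exact coverage.

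**The case against.** The strongest reply is that this is silence and not error. The article condenses a fuller plan, the bootstrap method is cited and not described, and a health-economics plan may settle the resampling unit. The investigators clearly know about clustering: they use an ICC for older people, model site for the clinical outcomes, and will report to the CONSORT extension for cluster trials. Expressing cost per participant is normal in cluster trials and does not imply independence.

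Much of this stands. A reader might infer that the plan prescribes a participant-level bootstrap and that its intervals will be 2.2 times too narrow. The documents do not support that: the unit is unstated, and 2.2 carries the ASCOT planning ICC over to quantities with no stated ICC. The factor also cannot be applied to an acceptability curve, which plots a probability against willingness to pay; such a curve can be too steep, but it has no width to divide by 2.2. Nor does the article say that the economic results will decide wider roll-out. The Discussion ties refinements before national implementation to the process evaluation.

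What does not stand is that the omission is harmless. The article states the site term for the clinical outcomes at the same level of detail. It also leaves the ICC out of the health-provider sample size, so allowance for clustering cannot be presumed everywhere. And the point does not turn on guessing the unit, since both plain readings under-cover.

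**Conclusion.** The concern holds in conditional form. The economic section rests its intervals and curves on a bootstrap with no stated allowance for site. If participants are resampled as independent, standard errors of the mean cost and QALY differences are understated by 2.2 at ICC 0.1 and 40 per site, within a range of about 1.2 to 2.6 over ICC 0.01 to 0.10 and 40 to 60 per site. If whole sites are resampled without correction, the shortfall is smaller but remains. In either case the curves overstate certainty. These figures assume equal site sizes and the ICC range above. The point is worth correcting before analysis, but it concerns a secondary analysis and leaves the primary clinical comparison untouched.

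**What to change.** In Economic analysis, state the resampling scheme. One suitable choice is a two-stage bootstrap: draw sites within arm, then participants within site, keep each person's cost and QALY together, and apply a shrinkage correction for few clusters. The alternative is a bivariate mixed model for cost and QALY with a site random effect and a small-sample correction; that option was not simulated here. Derive both the intervals and the acceptability curves from whichever is chosen, and report the observed ICCs for costs and QALYs.

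This takes a sentence or two and some analysis code, with no new data and no design change. The downside is wider intervals and flatter curves, which is what 5 sites per arm can support. Even the two-stage method may fall a little below 95% if the ICC is near 0.1, and the report should say so.

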### Oversight and monitoring

A 6 monthly project Stakeholder Advisory Group will provide oversight and advice of the project. This will include those with lived experience of elder abuse, older people, family carers, health providers, service providers, educators, and advocacy groups experienced in elder abuse responses.

This project has been ethically reviewed and approved by Austin Health Human Research Ethics Office through the National Mutual Acceptance Scheme with governance approval to be provided by each hospital site. Any changes to the protocol will be submitted to the Austin Health Human Research Ethics Office and all site Human Research Ethics Offices and will be updated on the ANZCTR where necessary.

## Discussion

There is a need for high-quality trials with adequate statistical power and appropriate study characteristics to determine what is effective in preventing or reducing elder abuse [47]. Addressing this call, this will be one of the few multi-component elder abuse RCTs in the world.

Our pragmatic approach aims to improve elder abuse knowledge, screening, and response in as many subacute health providers as possible rather than to provide extensive, specialised, or advanced training to fewer health providers who are under increasing demands due to pressures on the health care system. Our rationale is that upskilling more healthcare providers will result in increased detection of elder abuse and better response and management with beneficial flow-on effects to older people.

As both the training and screening tool have been co-designed, we expect high rates of acceptability amongst health providers. However, our multi-method process evaluation will allow us to determine what refinements are needed prior to national implementation.

### Limitations

We will exclude patients who receive subacute care at home, despite this being an increasingly popular model of care. This minimises the risk of screening in the presence of a perpetrator, which would reduce the likelihood of disclosing abuse and may pose risks to the older person and/or care staff.

Second, we will exclude older adults without the capacity to consent to research participation to avoid seeking proxy consent from a substitute decision maker, which could include a perpetrator of abuse.

Finally, the recruitment of older people by site champions after randomisation introduces a risk of bias as site champions will know whether they are in the intervention or control arm. This common problem with cluster RCTs will be managed in the analytic strategy (e.g. through difference-in-differences techniques).

### Dissemination policy: trial results

Trial results will be disseminated by publication in scientific journals and conferences. Following publication, the findings will also be promoted through stakeholder and industry newsletters, social media, and a national stakeholder forum at completion of the trial and through networks of international researchers involved in the study. Results will be disseminated regardless of the direction or magnitude of the effect.

### Dissemination policy: authorship

Authorship will be based on substantive contributions to the design, conduct, interpretation, and reporting and will include the investigator team, core research team, and consumers involved in investigator meetings.

Site principal investigators will be granted authorship for their contributions to the trial. Site champions and the Stakeholder Advisory Group will be included in the acknowledgments. Professional writers will not be used.

### Dissemination policy: reproducible research

The trial protocol and anonymised participant-level dataset will be made available upon request.

### Trial status

Protocol version 3, 11 September 2023. Recruitment has commenced. The approximate date when recruitment will be completed is 29 August 2025.

## Conclusions

Elder abuse often goes unreported and undetected. Older people may not feel comfortable to disclose it, and health providers may not know how to screen for or respond to it. Our work is a valuable first step to improving the health provider response to addressing this pernicious social issue.

## Data Availability

All members of the research team will have access to the final dataset. Access to the de-identified datasets will be available from the project lead investigator on request.
